## Abstract

**Background:**

Patients with chronic autoimmune thyroiditis have impaired health-related quality of life. The thyroid gland has a high selenium concentration, and specific selenoprotein enzyme families are crucial to immune function, and catalyze thyroid hormone metabolism and redox processes in thyroid cells. Previous randomized controlled trials have found that selenium supplementation decreases thyroid-disease-specific antibody levels. We hypothesize that selenium might be beneficial in the treatment of chronic autoimmune thyroiditis.

**Methods/Design:**

The CATALYST trial is an investigator-initiated randomized, blinded, multicentre clinical trial of selenium supplementation versus placebo in patients with chronic autoimmune thyroiditis. Inclusion criteria: age ≥18 years; serum thyroid peroxidase antibody level ≥100 IU/ml within the previous 12 months; treatment with levothyroxine and written informed consent. Exclusion criteria: previous diagnosis of toxic nodular goitre, Graves’ hyperthyroidism, postpartum thyroiditis, Graves’ orbitopathy; previous antithyroid drug treatment, radioiodine therapy or thyroid surgery; immune-modulatory or other medication affecting thyroid function; pregnancy, planned pregnancy or breastfeeding; allergy towards any intervention or placebo component; intake of selenium supplementation >55 μg/day; inability to read or understand Danish or lack of informed consent. The trial will include 2 × 236 participants. The experimental intervention and control groups will receive 200 μg selenium-enriched yeast or matching placebo tablets daily for 12 months. The experimental supplement will be SelenoPrecise^®^. The primary outcome is thyroid-related quality of life assessed by the Thyroid Patient-Reported Outcome (ThyPRO) questionnaire. Secondary outcomes include serum thyroid peroxidase antibody concentration; serum triiodothyronine/thyroxine ratio; levothyroxine dosage; adverse reactions and serious adverse reactions and events.

**Discussion:**

In this pragmatic trial, participating patients follow their usual treatment at their usual hospitals. In order to collect high-quality data on the clinical course and quality of life, and to minimize missing data, an elaborate trial management system has been designed. 12 months intervention duration was selected in consideration of the primary outcome, thyroid-related quality of life.

**Trial registration:**

ClinicalTrials.gov ID: NCT02013479.

## Background

Chronic autoimmune thyroiditis (AIT), also known as chronic lymphocytic thyroiditis or Hashimoto’s thyroiditis, is a common autoimmune disease, which most often leads to impaired function of the thyroid gland [1]. Its aetiology is based on a complex and poorly understood interaction between genetic susceptibility [2] and a number of environmental triggers [3,4]. In Denmark, the overall yearly incidence of overt hypothyroidism, that is*,* decreased circulating thyroid hormone levels, has been estimated at 47.2/100,000 [5]. AIT has been estimated to account for around 85% of these patients and is 8 to 9 times more frequent in women than in men [5,6]. Thyroid hormone production declines slowly in patients with AIT, with 5% per year progressing to overt hypothyroidism [7]. Standard treatment of AIT is levothyroxine (LT4), based on its long half-life of 8 days and stable generation of triiodothyronine (T3) by deiodination in peripheral tissues [8]. The goal of treatment is to restore euthyroidism and resolve symptoms of hypothyroidism. This is generally accomplished by adjusting the dosage of LT4 to normalize serum thyrotropin (TSH) levels. With rare exceptions, LT4 treatment is lifelong in patients with AIT [9]. According to a comprehensive review from 2006, health-related quality of life (HRQL) is impaired in most patients with benign thyroid disorders. However, the authors emphasized limitations due to lack of a validated and standardized questionnaire for thyroid-related quality of life assessment [10]. Subsequently, we have developed such a thyroid-related quality of life questionnaire, ThyPRO, to overcome the shortcomings and lack of validation of earlier HRQL questionnaires [11-14].

Large-scale community-based studies have demonstrated impaired well-being in euthyroid patients on LT4 treatment for primary hypothyroidism, indicating that restoration of euthyroidism is not the only predictor of good quality of life in patients with AIT [15,16]. In fact, hypothyroidism, even when adequately treated, is associated with increased morbidity and mortality [17-20]. In a cross-sectional study, by investigators from our group, responses to ThyPRO were analyzed in relation to thyroid volume, thyroid function and thyroid autoantibodies. Results suggested that thyroid peroxidase antibody (TPO-Ab) positivity *per se* might be associated with symptomatic distress in patients with AIT [21].

Selenium is a nonmetal mineral, a trace element and an essential micronutrient, incorporated into selenoproteins as the 21st amino-acid, selenocysteine. Selenoproteins have a wide range of effects in, for example, redox homeostasis, immunity, reproduction and thyroid hormone metabolism [22]. The recommended daily selenium intake in Denmark is 50 μg and 40 μg for men and women, respectively, and it is believed that 10% of Danish adults would benefit from increasing their intake [23]. In a recent Danish study, serum selenium concentration was inversely associated with thyroid volume, supporting a role for selenium in the thyroid gland, which indeed has the highest selenium concentration of all tissues [22,24]. A number of selenoproteins are expressed in thyrocytes. The most important of these are the iodothyronine deiodinases (DIO1, DIO2) that catalyze the formation of T3 from T4, and the glutathione peroxidases (GPx1, GPx3, GPx4) that catalyze the removal of peroxides and protect the thyrocytes from oxidative stress [25]. Two randomized clinical trials have shown no effect of selenium supplementation on serum TSH and thyroid hormone concentrations in healthy adults, even in those with moderately deficient selenium status [26,27]. Meanwhile, in the majority of 13 randomized clinical trials, selenium, in various formulations, effectively decreased serum TPO-Ab concentrations in AIT patients [28-40]. Some of the trials also reported other beneficial effects, including improvements in quality of life, although with limited presentation of the data supporting this claim. However, a recent systematic review concluded that evidence to support or discard the efficacy of selenium supplementation in AIT patients is inadequate, and highlights the need of additional randomized placebo-controlled trials to investigate direct clinical outcomes, in order to aid clinical decision making [41].

Only two randomized clinical trials have investigated the effect of selenium supplementation in patients with Graves’ disease, the other major autoimmune thyroid disease. One trial concluded that patients with Graves’ hyperthyroidism who received selenium, in a formulation with multiple antioxidants and in addition to antithyroid drugs (ATDs), attained euthyroidism faster than patients treated with only ATDs [42]. The other trial evaluated the effect of 200 μg selenium selenite daily in 159 euthyroid patients with mild Graves’ orbitopathy, and demonstrated improved disease-specific quality of life and a reduced disease severity, as compared with placebo [43]. We are conducting a trial entitled ‘Selenium supplementation in patients with Graves’ hyperthyroidism (GRASS)’ (ClinicalTrials.gov NCT01611896). The purpose of the GRASS trial is to investigate whether selenium, in addition to the standard treatment with ATDs, in patients with Graves’ hyperthyroidism, will lead to a decrease in antithyroid treatment failure, faster remission and improved quality of life during the first year of treatment. Enrolment of 492 patients into the GRASS study was initiated in December 2012. Patients are randomized to intervention with 200 μg/day of selenium-enriched yeast versus placebo for 24 to 30 months. The CATALYST and GRASS trials are closely connected in terms of study design and will largely be performed by the same group of investigators. Therefore, some sections of the CATALYST protocol are identical to the GRASS protocol [44].

We hypothesize that the addition of selenium to the standard treatment with LT4 in patients with AIT may lead to an improved quality of life and reduce autoimmune disease activity.

## Methods/design

### Objectives

The primary objective is to investigate the effect of 12 months’ intervention with selenium supplementation compared with placebo in patients with AIT, on thyroid-related quality of life, as measured using the ThyPRO questionnaire.

Secondary objectives are to investigate the effect of selenium supplementation compared with placebo on: LT4 dosage; serum T3/T4-ratio; serum TPO-Ab concentration; plasma selenium concentration; and immunological and oxidative stress biomarkers. Monitoring adverse and serious adverse events and reactions constitute additional secondary objectives.

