### Trial intervention

#### **
*Selenium*
**

In this trial, oral tablets of selenium-enriched yeast will be used. The experimental intervention will be 200 μg selenium per day, corresponding to two 100 μg tablets SelenoPrecise^®^ in a formulation registered as a dietary supplement and produced by Pharma Nord ApS, Vejle, Denmark.

#### **
*Placebo*
**

The control intervention will be two placebo tablets per day as inactive spray-dried baker’s yeast, comprising 250 mg yeast placebo, 80 mg cellulose, 65 mg dicalcium phosphate, and ≤5 mg other inactive ingredients. Tablets will be identical to the experimental intervention as regards size, appearance, taste, smell and solubility and will be produced by Pharma Nord ApS, Vejle, Denmark.

#### **
*The trial data management system (TDMS)*
**

Since the design will involve limited interaction between participants and trial personnel, a considerable part of the data collection, trial conduct, trial surveillance and timing, is handled by a trial data management system TDMS. This system, named PROgmatic, is described in detail in an independent publication [45]. It consists of a patient-survey interface, a trial-personnel interface, a system-integration interface and a program ‘motor’. The system features include secure web-based data entry; electronic case report forms (eCRFs); central participant registration and randomization; automated emails linking to electronic patient-reported outcomes; automated reminders to participants; automated notifications to trial personnel regarding booking of trial visits, safety and compliance alerts and monitoring of trial progress. It will be used for collecting outcome data, adverse events, and other study-relevant information; for timing of trial events, that is, time for patient-reported outcomes and trial visits; for identification of need for action (for example, contact to a participant); and for delivery of output to personnel or participants (for example, email notifications). In this way, the eCRFs are created by integration of patient-input, trial-personnel input and collection of electronic data regarding biochemical analyses (that is, blood-tests taken as part of the usual routine). All activities are automatically logged. The TDMS complies with the security policies of the participating hospitals and the Act on Processing of Personal Data, and is approved by the Danish Data Protection Agency.

#### **
*Randomization*
**

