### Outcomes

Data will be collected for outcome assessment at six specified times during the trial (Table 1).

**Table 1 T1:** Timing of data collection

**Variable**	**Inclusion baseline**	**Follow-up 6 weeks ± 1 week**	**Follow-up 3 months ± 2 weeks**	**Follow-up 6 months ± 2 weeks**	**Follow-up 12 months ± 2 weeks**	**Follow-up 18 months ± 2 weeks**
Visit	*x*		*x*		*x*	*x*
Weight	*x*_ *v* _		*x*_ *v* _		*x*_ *v* _	*x*_ *v* _
Medical treatment	*x*_ *v* _		*x*_ *v* _		*x*_ *v* _	*x*_ *v* _
ThyPRO	*x*_ *r* _	*x*_ *r* _	*x*_ *r* _	*x*_ *r* _	*x*_ *r* _	*x*_ *r* _
TSH, FT4, FT3	*x*_ *s* _		*x*_ *s* _		*x*_ *s* _	*x*_ *s* _
TPO-Ab	*x*_ *s* _		*x*_ *s* _		*x*_ *s* _	*x*_ *s,* _
LT4 dosage	*x*_ *v* _		*x*_ *v* _		*x*_ *v* _	*x*_ *v* _
Immunological and oxidative stress biomarkers	*x*_ *s* _		*x*_ *s* _		*x*_ *s* _	*x*_ *s* _
Selenium	*x*_ *s* _		*x*_ *s* _		*x*_ *s* _	*x*_ *s* _
Creatinine/iodine ratio in spot urine	*x*_ *s* _					
Tablet count			*x*_ *v* _		*x*_ *v* _	
Consumption of additional selenium	*x*_ *v* _		*x*_ *v* _		*x*_ *v* _	*x*_ *v* _
Adverse reactions			*x*_ *v* _		*x*_ *v* _	*x*_ *v* _
Serious adverse reactions and events (SARs, SUSARs and SAEs)						*x*_ *p* _

All assessments must be made at the time points specified above. If not possible at the specified time, the assessment shall still be conducted, and the time of assessment shall be noted in the specified electronic case report form (eCRF). *x*_
*v*
_, analyzed via data obtained in eCRFs at trial visits, administered through the trial data management system (TDMS); *x*_
*r*
_, analyzed via patient-reported outcomes, administered through the TDMS; *x*_
*s*
_, analyzed in blood or urine samples obtained at trial visits; *x*_
*p*
_, analyzed via public national registries at the end of the trial.

#### **
*Primary outcome*
**

Improved thyroid-related quality of life during the 12 months intervention after randomization, as measured by one composite score from the ThyPRO questionnaire [49].

#### **
*Secondary outcomes*
**

Secondary outcome assessment is specified in Table 1. Forkhead Box P3 mRNA will be measured as an immunological biomarker, and urinary 8-oxo-2'-deoxyguanosine and 8-oxoguanine will be measured as oxidative stress biomarkers.

#### **
*Assessment of adverse reactions and events*
**

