The latest version of the SPC shall at all times be used for the assessment of adverse reactions (ARs), which will be reported as a secondary trial outcome. Participants are questioned about ARs according to Table 1. In addition, participants are instructed to contact their trial contact person if they experience symptoms suggestive of ARs.

In the assessment and reporting of serious adverse reactions (SARs), serious unexpected serious adverse reaction (SUSARs) and serious adverse events (SAEs), data on hospital admissions and mortality will be obtained through national registries at the end of the trial. Also, participants are informed and instructed to contact their trial contact person if they are admitted to a hospital for selenium intoxication, experience a clinical picture indicative of selenium intoxication, or experience a clinical picture that is unexpected but suspected to be related to selenium intoxication. When a possible serious event (SAE, SAR or SUSAR) is identified, details will be sought from the patient’s medical record and through direct contact with the patient. Any SAE, SAR or SUSAR will be reported as an outcome measure.

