Analyses will be performed using SAS (SAS Institute Inc. ©, Cary, NC, USA), version 9.3 or later. All analyses will be intention-to-treat analyses performed blinded with the two intervention groups concealed as, for example, ‘A’ and ‘B’. Significance tests will be at the 5% level and two-sided. Table 2 shows, for each outcome, its priority, when it will be measured, the mathematical type of measure, and the analytical procedure to be used when analyzing the outcome values. The analytical procedures and handling of missing values are described next.

**Table 2 T2:** Outcome measures

**Outcome (priority)**	**Times of measurements**	**Mathematical type of quantity (analytical category)**
ThyPRO composite scale score (P)	Time sequence of six measurements^a^	Numerical (1 + 2)
ThyPRO hypothyroid symptoms (S)	Time sequence of six measurements^a^	Numerical (1 + 2)
ThyPRO goitre symptoms (S)	Time sequence of six measurements^a^	Numerical (1 + 2)
LT4 dosage (S)	Time sequence of four measurements^b^	Numerical (1 + 2)
Serum TPO-Ab (S)	Time sequence of four measurements^b^	Numerical (1 + 2)
Serum FT3/FT4 Ratio (S)	Time sequence of four measurements^b^	Numerical (1 + 2)
Plasma selenium (S)	Time sequence of four measurements^b^	Numerical (1 + 2)
Biomarkers of immunology and oxidative stress (S)	Time sequence of four measurements^b^	Numerical (1 + 2)
Adverse reactions (S)	End of trial	Rate (3)
Serious adverse events (S)	End of trial	Rate (3)

Outcomes with priorities, times of measurement and mathematical types of quantity with analytical categories. P, primary outcome measure; S, secondary outcome measure. Analytical categories 1 to 3 are defined in the main text. ^a^, includes five measurements relative to the reference time (6 weeks, 3 months, 6 months, 12 months and 18 months after randomization); ^b^, includes three measurements relative to the reference time (3 months, 12 months and 18 months after randomization).

#### **
*Analytical procedures*
**

Depending on the specific analytical category of each outcome measure, one or two of three types of regression analyses will be applied (Table 2).

#### **
*Analytical categories*
**

*Type 1* includes a continuous outcome measure (*y*) measured 3 to 6 times at 6 weeks, 3, 6, 12 or 18 months after randomization. It is viewed as a linear function of time (*t*). The model is:

*y* = *a* + *b***I* + *c***t* + *d***I***t*

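### Adverse events are a stated monitoring objective, but non-serious events not judged to be reactions have no schedule row, outcome row or planned comparison between arms

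*Protocol article*

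**What the plan says.** The Objectives section of the protocol article lists the effects to be compared with placebo and then adds: "Monitoring adverse and serious adverse events and reactions constitute additional secondary objectives". Events are named there alongside reactions. The section on the trial data management system says of that system: "It will be used for collecting outcome data, adverse events, and other study-relevant information". The Discussion also describes monitoring of both reactions and events, through instructions to participants, responses to system prompts, and national hospitalisation data.

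The operational sections are narrower:

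- **Assessment of adverse reactions and events:** "The latest version of the SPC shall at all times be used for the assessment of adverse reactions (ARs"), and "Participants are questioned about ARs according to Table 1". Between visits, "participants are instructed to contact their trial contact person if they experience symptoms suggestive of ARs".
- **Table 1 (schedule):** there are two safety rows. One is adverse reactions, at 3, 12 and 18 months. The other is "Serious adverse reactions and events (SARs, SUSARs and SAEs"), taken from registries at the end of the trial.
- **Table 2 (outcomes and analyses):** there are two safety rows, "Adverse reactions (S") and "Serious adverse events (S"), both secondary and both analysed as rates (type 3: Poisson regression with log follow-up period as offset).
- **Abstract:** the safety outcomes are adverse reactions, serious adverse reactions and serious adverse events.

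**The concern.** In a blinded, placebo-controlled trial, the difference between arms shows what the supplement causes. A count restricted to events already attributed to the supplement puts an individual causality judgement ahead of that comparison. Attribution works well for known effects. It works poorly for an effect nobody expects, which is the kind that only the randomised comparison can reveal.

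The Safety section describes the SPC profile as mainly gastrointestinal and dermatological. It supports the tablet with a trial in 501 general-practice volunteers, citing selenium levels after 6 months. The present participants have autoimmune thyroiditis, take levothyroxine and receive the intervention for 12 months. If a non-serious harm outside the familiar profile occurred, the plan as written would not commit the trial to comparing it between arms, although the Objectives section names adverse events.

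**Working it through.** **Step 1: set the sections side by side.**

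| Place in the article | Non-serious adverse events, whatever the cause | Adverse reactions | Serious events |
|---|---|---|---|
| Objectives | named (events and reactions) | named | named |
| Data management system | adverse events collected | not separately named | not separately named |
| Discussion | monitoring of events described | described | hospitalisation data |
| Abstract, secondary outcomes | absent | listed | listed |
| Table 1 | no row | row at 3, 12, 18 months | row, registries |
| Assessment section | not asked about | asked about, assessed with the SPC | registries, contact, records |
| Table 2 | no row | row, type 3 | row, type 3 |

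None of the 2 safety rows in Table 1, and none of the 2 in Table 2, covers non-serious events irrespective of cause. Table 2 is introduced as giving priority, timing and analysis for each outcome, so the missing row means that no comparison is planned.

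**Step 2: what the SPC does.** The assessment section says that the current SPC is used to assess reactions. It does not say whether an unlisted non-serious symptom can be recorded as a reaction. The only explicit route for something unexpected that participants are told to report is a clinical picture suspected to be related to selenium intoxication, which is itself conditional on attribution.

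**Step 3: size.** The article states no safety rate or safety power, so there is no figure of its own to reproduce. What follows is illustration only, and every rate in it is assumed.

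Inputs: n = 236 per arm (sample size section), two-sided 5% test; assumed true proportions with the event p0 = 5% on placebo and p1 = 12% on selenium; assumed share *a* of events attributed and recorded, equal in both arms.

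Formula: power = Φ[(d − 1.96·SE0)/SE1], with d = a(p1 − p0). SE0 is the pooled and SE1 the unpooled standard error of the difference between the recorded proportions.

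For a = 1: d = 0.07, SE0 = 0.02567, SE1 = 0.02547; (0.07 − 0.0503)/0.02547 = 0.77, so power is 78%.

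| Share recorded | Recorded proportions | Expected participants | Ratio | Power |
|---|---|---|---|---|
| all | 5% vs 12% | 11.8 vs 28.3 | 2.4 | 78% |
| half | 2.5% vs 6% | 5.9 vs 14.2 | 2.4 | 47% |
| a quarter | 1.25% vs 3% | 3.0 vs 7.1 | 2.4 | 26% |
| a tenth | 0.5% vs 1.2% | 1.2 vs 2.8 | 2.4 | 13% |

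The ratio does not move; only counts and power fall. This compares proportions, whereas Table 2 plans Poisson rates, so it shows the direction of the loss and is not a power statement for the trial.

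**The case against.** **The objective can be read more narrowly.** The Objectives section separates effects compared with placebo from the monitoring of harms, and only the former expressly promises a comparison. The monitoring phrase could also be shorthand for the Abstract's list, which matches both tables. This has some force: it is not established that the trial must fail its objective. But the wording names events, the data management section says they are collected, and Table 2 gives them no analysis. The sections still need reconciling.

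**A reader might infer that such harms cannot be detected, or that no data would exist.** The article does not support that. The data management section says that adverse events are collected, and the Discussion describes surveillance through prompts. What is absent is a schedule row, an outcome row and a pre-specified comparison.

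**A reader might infer that only SPC-listed symptoms count.** That is not stated. The article also provides for serious unexpected reactions, so it recognises reactions beyond a known list, at least among serious ones. The supported point is that the handling of unlisted non-serious symptoms is unclear.

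**A reader might infer that a finding of no excess is partly built in, or that a changing SPC distorts the result.** Blinding should make attribution similar in both arms, so filtering lowers counts and power without by itself pulling the rate ratio to one. Nothing shows that the SPC would change. If it did, both concurrently randomised arms would be affected alike.

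**Some symptoms are compared whatever their cause.** ThyPRO is collected from all participants, and its composite, hypothyroid-symptom and goitre-symptom scores are compared between arms. This is true, but it covers thyroid-related complaints only.

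**Proportionality.** This is a pragmatic trial of a dietary supplement with limited contact between participants and staff, and an article may leave form wording to the full protocol. The absence of form detail is accordingly no criticism here. The point is the mismatch between sections that the article does spell out.

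**Conclusion.** The point holds as an internal mismatch with a practical consequence. Adverse events are named as something to monitor and to collect. Yet non-serious events not judged to be reactions appear in neither table and have no planned comparison by arm, and the SPC's role for unlisted symptoms is undefined. The consequence is reduced coverage and power for unanticipated non-serious harms, not bias in the comparison of what is recorded. That last conclusion assumes that blinding holds and that attribution works alike in both arms. The size cannot be derived from the article. Under the assumed 5% versus 12%, power would fall from 78% with full recording to 47% if half the events were attributed and 13% if a tenth were. This is a worthwhile and inexpensive improvement; it does not threaten the primary analysis.

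**What to change.** Reconcile the Objectives, the data management section, Table 1, the assessment section, Table 2 and the Discussion (and the Abstract's list with them):

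1. At the 3-, 12- and 18-month visits where participants are already questioned, record every adverse event regardless of suspected cause. Amend the Table 1 row to match.
2. Classify relatedness afterwards, as a separate step from recording.
3. Add all non-serious adverse events to Table 2 as a secondary safety outcome compared between arms with the existing type 3 analysis.
4. Keep adverse reactions as a subset, and state that a symptom need not be listed in the SPC to be recorded.

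The cost is a change of wording and case report form fields, with no extra visits. The downside is more entries to record and code across 472 participants, many of them unrelated to selenium. The change is best made before visits begin, because events not recorded at a visit cannot be reliably recovered later.
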